**Fig. 2 Fig2:**
[figure not shown]
Timeline for household visits and telephone calls for mothers from the intervention group

At 6, 12 and 24 months of age, all study children (intervention and control group) will have measured for five days the duration of self-regulated nighttime sleep by means of actigraphy. At 12 and 24 months of age all study children (intervention and control group) will undergo anthropometry and neurodevelopment assessment. Figure 3 shows the timeline for outcome evaluations.

**Fig. 3 Fig3:**
[figure not shown]
Timeline for study outcomes

### Study team

The fieldwork team is composed of visitors, interviewers, fieldwork supervisors, and coordinators. All visitors were females with graduation in Nursing, Nutrition or Pedagogy. Visitors training included general instructions in regard to the study protocol, reading of the questionnaire and fieldwork manual, detailed discussion of each question, and practice questionnaire administration among themselves and with volunteer mothers (not participating in the study). Special focus was given to the training of visitors on the delivery of the intervention: written training material focusing on normal sleep behaviors, how to facilitate sleep onset and how to manage night awakenings were produced to the intervention training. Two Pediatricians, two Psychologists, one Nutritionist and one Geneticist were the Facilitators at the training sections. The training program lasted 48 h, with 75 % of the time spent in practical sessions with volunteer mothers not belonging to the Pelotas 2015 Birth Cohort. The development of counseling skills was emphasized. The performance of all trainees was formally assessed at the end of the training to document its effectiveness and to aid the coordinators in the selection of the fieldworkers. For standardization proposals, the visitors were re-trained in the content and delivery of the intervention three months after the start of the fieldwork.

All interviewers have completed university level graduation. About twice the number of interviewers necessary for each visit are included in the training program. Interviewer selection is based on a written test and performance evaluation during training. The anthropometric measures are performed by the 2015 cohort fieldworkers that received specific anthropometry techniques training for assessing children aged 3, 12 and 24 months at a daycare center, until all of them were performing measurements correctly. The maximum allowed differences for acceptable precision for length is 7 mm, for weight 50 g in neonates and 100 g in older infants.

### Quality control

Quality control measures include use of pretested, standardized data collection forms; the construction of detailed visitor and interviewer guides; careful selection and evaluation of visitors and interviewers; thorough training on interviewing and anthropometric measurements, followed by standardization sessions with assessment of intra and inter-observer variability; weekly meetings of fieldwork supervisors with the visitors and interviewers; double data entry; and range checks for data values. Additionally, at a daily basis visitors and interviewers send electronically a report of the work performed during the day to the fieldwork supervisor that gives them any needed feedback.

### Pilot study

Prior to the study start, the sleep recommendations were tested in a pilot group of 20 mothers of children at the first year of life. The aim of the pilot study was to evaluate the acceptability of the recommendations and the feasibility of the study in the cultural context of child care practices in the city of Pelotas and to undertake the appropriate adjustments if necessary.

### Methodology of analysis

The intervention and control groups will be compared in terms of baseline indicators collected at the perinatal cohort interview and at the 3-month cohort interview, including child sleep habits at 3 months of age. Any differences between the two groups that had occurred despite the randomization will be adjusted for in the analyses. Analyses will be completed on an intention-to-treat basis. The Stata Statistical Software will be used in the analyses. Trial results will be communicated to healthcare professionals and other relevant groups via scientific publications in open-access peer-reviewed medical journals. To communicate the results to the community press release to local and regional newspapers containing the relevant findings of the study will be written.

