### Sample size

The following parameters were set for sample size calculation: 95 % confidence interval; double-sided statistical tests; 80 % power; 1:1 ratio of intervention to control group; average self-regulated sleep period duration in the control group at 6 months as 9.70 ± 1.98 h, [18] 10.25 ± 1.90 h at 12 months, [18], and 10.30 ± 1.26 h at 24 months; [19] and self-regulated night sleep at least 30 min longer in the intervention group at 6, 12 and 24 months when compared to the control group. The greatest sample size obtained was 251 children in each group. With an added 10 % to account for losses to follow-up and for adjustments in the analyses the final number of children per arm is 276.

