## Outcomes definition

### Primary outcome

The main outcome is the average duration of nighttime self-regulated sleep (the maximum amount of time the child stays asleep or awake without awakening the parents), [18] at ages 6, 12 and 24 months. This outcome will be evaluated using actigraphy and sleep activity diary records (5 consecutive days before the intervention - baseline assessment) and for 5 consecutive days at ages 6, 12 and 24 months.

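### Covariates for the outcome analyses are chosen by observed baseline imbalance, with no criterion or list, and the pre-allocation sleep recording is given no role in the model

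*Protocol article*

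**What the plan says.** The protocol article, under Methodology of analysis, sets out two steps. First, "The intervention and control groups will be compared in terms of baseline indicators collected at the perinatal cohort interview" and at the 3-month cohort interview, with child sleep habits at 3 months among the items. Second, "Any differences between the two groups that had occurred despite the randomization will be adjusted for in the analyses". It gives no threshold or other criterion for a difference, and no list of covariates.

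Under Primary outcome, the same article plans actigraphy and a sleep diary for "5 consecutive days before the intervention - baseline assessment", and again at 6, 12 and 24 months. The sections on actigraphy, the 5-day diary and study logistics show that this first recording is planned for all enrolled children, in both arms, before the allocation envelope is opened. No section says how it enters the comparison of the arms.

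**The concern.** Under sound randomisation, baseline differences between arms are due to chance. Their size says nothing about whether a variable predicts the outcome, and prediction is what makes a covariate worth including. A rule driven by imbalance can admit variables unrelated to sleep and leave out strong predictors that happen to be balanced.

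The wording also leaves the choice open. The Questionnaires section lists many family, perinatal and infant items, and the Brief Infant Sleep Questionnaire adds more. Without a criterion, two analysts following the sentence could adjust for different sets and report different estimates, each consistent with the protocol. The choice would be made with data by arm in view.

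Finally, a pre-allocation recording of sleep by the outcome instruments is a natural candidate for the primary covariate. It is already being collected, yet the plan does not commit to using it.

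**Working it through.** **Inputs, all from the Sample size section.** The design is "double-sided statistical tests; 80 % power; 1:1 ratio of intervention to control group", with alpha 0.05 from the 95% confidence interval. Control values are "average self-regulated sleep period duration in the control group at 6 months as 9.70 ± 1.98 h", "10.25 ± 1.90 h at 12 months" and "10.30 ± 1.26 h at 24 months". The target is "self-regulated night sleep at least 30 min longer in the intervention group at 6, 12 and 24 months", so 0.5 h. The stated size is 251 per arm, raised by 10% to 276.

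**Step 1: reproduce the stated size.** n per arm = 2 × (1.960 + 0.842)² × SD² / 0.5².
- SD 1.98: 246.2, so 247
- SD 1.90: 226.7, so 227
- SD 1.26: 99.7, so 100

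Six months governs, as the article implies. The stated 251 is within 2% of 247, and an SD rounded to 2.0 gives 251.2. The inflation also matches: 251 × 1.10 = 276.1.

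**Step 2: unadjusted power at 251 per arm.** Power = Φ(0.5 / (SD × √(2/251)) − 1.960).
- 6 months: Φ(2.829 − 1.960) = 80.8%
- 12 months: Φ(2.948 − 1.960) = 83.9%
- 24 months: Φ(4.446 − 1.960) = 99.3%

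**Step 3: always adjust for baseline sleep.** Adjustment reduces the residual SD to SD × √(1 − r²), where r is the correlation between baseline and outcome. The documents give no r, so a range is assumed. For 6 months (SD 1.98):

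| r (assumed) | Residual SD | n per arm for 80% | Power at 251 per arm |
|---|---|---|---|
| 0 | 1.98 | 247 | 80.8% |
| 0.1 | 1.97 | 244 | 81.1% |
| 0.3 | 1.89 | 225 | 84.3% |
| 0.5 | 1.71 | 185 | 90.4% |
| 0.7 | 1.41 | 126 | 97.7% |

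**Step 4: adjust only if imbalanced.** This was simulated at 251 per arm with 40,000 trials per setting and one baseline variable. Adjustment was triggered when the arms differed at p < 0.05; this trigger is an assumption, because the article states none.

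| r (assumed) | Power, unadjusted | Power, if imbalanced | Power, always adjusted | Type I error, if imbalanced |
|---|---|---|---|---|
| 0.1 | 80.6% | 80.6% | 80.9% | 5.1% |
| 0.3 | 80.5% | 80.9% | 84.0% | 4.8% |
| 0.5 | 80.7% | 81.7% | 90.2% | 4.2% |
| 0.7 | 80.4% | 82.4% | 97.6% | 3.6% |

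The rule triggers adjustment in about 5% of trials, so it captures little of whatever gain exists. Always adjusting keeps the type I error at 5.0 to 5.1%.

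**The case against.** The strongest reply is that a condensed article may leave the exact outcome model to an analysis plan that is not shown. That holds for what the article does not mention, including the role of the actigraphy and diary baseline. It does not cover the imbalance rule, which the article states outright; an analysis plan that fixed covariates in advance would depart from that sentence.

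Several stronger readings are tempting, and the documents do not support them.

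- *Baseline actigraphy is adjusted for only if it is imbalanced, or has been rejected as a covariate.* The rule as worded screens cohort interview items only, and the actigraphy and diary are collected separately after consent. Their role is unstated. The Discussion speaks of comparing sleep before and after the intervention, which suggests some use.
- *The trial is underpowered.* It is sized to reach its 80% target without adjustment. What may be forgone is extra precision, and at r = 0.1 that is under one percentage point. Sleep at 3 months may correlate weakly with sleep at 12 or 24 months.
- *The rule inflates false positives.* With one baseline variable, the simulation shows error from nominal to conservative. The risk from a free choice among many covariates is real but is not quantified here.
- *Some indicator will very probably trigger adjustment.* With 20 independent indicators and a p < 0.05 trigger, the chance is 1 − 0.95²⁰ = 64%. The plan states neither the number, nor independence, nor any significance test, so this only illustrates the problem.
- *Length at 3 months must be added to the growth analysis.* Conditional linear growth, as the term is normally used, already accounts for earlier length.

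**Conclusion.** The point stands as a badly fixed method that should be changed. The article commits the analysis to covariates chosen by observed imbalance, without a criterion or list. The primary model is therefore unknown until data by arm are seen, whatever the correlation between baseline and later sleep.

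The loss of precision is a secondary matter of uncertain size. At 6 months, prespecified baseline adjustment would raise power from about 81% by anything from under 1 point (r = 0.1) to about 17 points (r = 0.7), with about 3 points at 0.3 and 10 at 0.5. At 24 months unadjusted power already exceeds 99%, so there is essentially nothing to gain. These figures rest on the article's SDs, 251 analysed children per arm, a usable baseline for each child and assumed correlations.

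**What to change.** Replace the imbalance sentence under Methodology of analysis with a rule along these lines: the primary analysis regresses nighttime self-regulated sleep on arm, adjusted in every case for the baseline value of the same measure from the same instrument, plus at most a short list of prognostic covariates named now. Missing baseline values are handled by mean imputation or a missing indicator, so that no child is dropped for a failed recording. Baseline tables are descriptive only, and any model with covariates chosen by imbalance is labelled a sensitivity analysis.

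The cost is mainly wording. The baseline recordings are already planned and the sample size need not change. One definition has to be settled first. The article assigns actigraphy, diary and questionnaire to a single outcome, and the actigraphy variables it lists do not include self-regulated sleep by name. The baseline covariate must be defined from the instrument that supplies the primary outcome.

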## Discussion

The proposed study has strengths and limitations. One of the strengths is its feasibility. A population-based birth cohort study initiated in the same city in 2004 showed that an average of 300 children are born each month from mothers residing in the urban area of Pelotas at the city hospitals, [31] and that the mean total sleep duration (sum of daytime and nighttime) at age 3 months was 13.34 ± 2.91 h (data not published). Therefore, it was possible to obtain the necessary number of children during the year 2015 within the ongoing birth cohort study. To enable proper follow-up within the schedule of the proposal, children born between July, 1^st^ and December, 31^st^, 2015 were eligible to the trial.

This project is focused on sleep duration. The literature, especially observational studies, often does not distinguish between time in bed and actual sleep time. However, actual sleep time is typically less than time in bed, which biases data toward higher sleep duration estimates. By contrast, intervention studies using laboratory measured sleep time typically produce shorter sleep durations. This study will employ maternal records (diaries) and actigraphy to measure and compare sleep habits between intervention and control group before and after the delivery of the intervention. Those are reliable and recommended methods to assess the effect of interventions aiming to improve child sleep [7].

Additionally, as this trial is nested within a birth cohort, it will be possible to follow the trial participants in the future and assess long-term effects of the intervention, such as attained height, academic achievement, intelligence quotient, mental health, and economic productivity in adult life.

Because this is an efficacy trial, maternal compliance is mandatory for the achievement of the study objectives. However, poor maternal adherence to the recommended practices is a potential limitation of this study. After the delivery of the recommendations, mothers from the intervention group received telephone calls in two consecutive days and one additional home visit (at day 8 after the randomization) as a strategy to promote compliance. The use of diaries to record the number of nighttime awakenings, duration of nighttime awakenings, and measures undertaken to aid the child back to sleep will help to measure maternal compliance with the study. The booklet containing key messages of the intervention will help the mother remember the recommendations. Also, a telephone number to contact the study team was provided to support mothers in the implementation of the recommendations that are part of the intervention. The main outcome (self-regulated night sleep) will be assessed by maternal report, diaries and, in order to prevent information bias, by means of an objective measure (actigraphy).

It is expected that this study will demonstrate the beneficial effect of a sleep intervention on children’s sleep behavior. This is a low cost intervention that does not require specialized professional to be delivered and that can be scaled-up to high-, middle- and low-income countries. The negative impact of inadequate and insufficient sleep on children’s physical and mental health are unquestionable, as well as its impact on cognitive function, academic performance and behavior, all of these being factors to which children in low- and middle-income countries are at higher risk [32]. Behavioral interventions targeting mothers and young children that can be delivered inexpensively and that do not require specialized training can help prevent future issues by reducing the risk to which these children are exposed.

## Abbreviations

BISQ: Brief Infant Sleep Questionnaire
CF: Consent form
GH: Growth hormone
INTER-NDA: The Intergrowth Neurodevelopment Assessment tool
OX-NDA: The Oxford Neurodevelopment Assessment tool
